## Abstract

**Background:**

In the management of patients with *RAS* wild-type metastatic colorectal cancer (mCRC), anti-epidermal growth factor receptor (EGFR) therapies have demonstrated a clinical benefit, with longer survival. However, the correlation between the emergence of circulating *RAS* mutations and secondary resistance to anti-EGFR therapies requires further elucidation. In this study, we aim to examine evolutionary changes in *RAS* mutations through liquid biopsy in patients with mCRC during and after anti-EGFR therapy.

**Methods:**

A total of 120 patients diagnosed with *RAS* wild-type mCRC will be enrolled in this study. Patients will receive a cetuximab-based infusional 5-fluorouracil regimen as first-line treatment. Cetuximab-based treatment is expected to continue until disease progression, intolerable toxic effects, or withdrawal of consent. Blood samples from enrolled patients will be collected before and then every 3 months during cetuximab-based treatment and also at disease progression. These blood samples will be evaluated for *RAS* resistance mutations by using the MassARRAY platform. The primary endpoint is the percentage of *RAS* mutations detected in circulating DNA from patients during cetuximab treatment. The correlation between the tumor response and survival outcomes of these patients and the emergence of circulating *RAS* mutations will be further analyzed.

**Discussion:**

Liquid biopsy is a powerful technology that can represent tumor heterogeneity in a relatively noninvasive manner. Because *RAS* mutations play a major role in resistance to anti-EGFR therapy for mCRC, examining evolutionary changes in these mutations during such treatment through liquid biopsy would be useful. After comprehensively analyzing the emergence of circulating *RAS* mutations and its clinical relevance in this study, our results should provide practical guidance on anti-EGFR therapy for mCRC.

**Trial registration:**

The date of trial registration (NCT03401957) in this study was January 17, 2018.

**Electronic supplementary material:**

The online version of this article (10.1186/s12885-019-5826-7) contains supplementary material, which is available to authorized users.

## Background

Colorectal cancer (CRC), a neoplasm arising from the large bowel, is a common and lethal disease with approximately 1,100,000 new cases and 550,000 deaths worldwide in 2018 [1]. In Taiwan, CRC is the most commonly diagnosed cancer (15,579 new cases in 2015) and the third most common cause of cancer-related deaths (5687 deaths in 2015) [2]. Nearly 20% of newly diagnosed cases of CRC are metastatic at initial presentation; a certain proportion of patients in early stages would also develop metastases even after curative surgery [3]. Systemic treatment is generally recommended for metastatic CRC (mCRC). In addition to conventional chemotherapy drugs, several agents targeting the molecular drivers of CRC pathogenesis, including signaling pathways mediated by the epidermal growth factor receptor (EGFR) and vascular endothelial growth factor, have been applied in such patients, with increasing survival rates [4–8].

Cetuximab is an EGFR-targeted monoclonal antibody with established clinical benefits as a component of first-line treatment for patients with *RAS* wild-type mCRC [7, 8]. The predictive role of *RAS* mutations in the clinical responses of mCRC to anti-EGFR therapies has been demonstrated in several pivotal studies [7–11]. RAS belongs to a family of small G proteins, including HRAS, KRAS, and NRAS, which are responsible for ligand-dependent receptor activation. In general, *KRAS* mutations are found in approximately 40% of patients with CRC, *NRAS* mutations are about 3%, and *HRAS* mutations are relatively rare [11, 12]. Mutations at key sites within the *RAS* family cause constitutive activation of RAS-associated signaling, rendering anti-EGFR therapies ineffective for mCRC. Therefore, the identification of *RAS* mutations in tumor tissues to determine patients that are more likely to benefit from anti-EGFR therapies has become standard in the pretreatment management of patients with mCRC [12]. Moreover, acquired resistance inevitably appears in some patients after the initial response to cetuximab, thus limiting the clinical benefit of this anti-EGFR antibody. The emergence of *RAS* mutations is also potentially responsible for acquired resistance to cetuximab in patients with mCRC [13–15]. *RAS* mutations have been identified after anti-EGFR therapies in approximately 50% of patients with *RAS* wild-type mCRC [13, 14]. In addition, genetic alterations in *BRAF*, a downstream effector of the EGFR signaling pathway, have been found in around 5% of patients with CRC. Some meta-analyses have shown that *BRAF*-mutant CRCs are associated with the low clinical efficacy of anti-EGFR therapies [11, 12]. Accordingly, dynamic monitoring for the emergence of activation mutations of effectors downstream located in EGFR signaling pathway, especially *RAS* mutations in patients undergoing anti-EGFR therapies can be a useful tool to determine tumor response and ongoing patient care.

During cancer progression, circulating nucleic acids carrying specific genetic alterations of tumor cells (circulating tumor DNA, or ctDNA) from both primary and metastatic sites can enter the bloodstream [16]. Liquid biopsy is a newly developed technique capable of detecting these genetic alterations, especially specific base nucleotide substitutions from ctDNA, through blood sampling. Certain point mutations of tumor cells from circulating free DNA (cfDNA) in the plasma of patients with a given cancer type, including CRC, have been identified [17, 18]. An analysis of cfDNA through liquid biopsy avoids the limitations of tumor tissue-based mutation analysis. Therefore, this minimally invasive technique can offer the advantage of continuously monitoring the major genotype represented in tumor cells with a complex heterogeneity. Nevertheless, substantial challenges remain because ctDNA often represents only a small fraction of total cfDNA [19–21]. Standard sequencing approaches, such as the Sanger sequencing method, can only detect tumor-specific mutations in patients with a heavy tumor burden. A personalized approach using sensitive detection tools, such as next generation sequencing (NGS), is also not feasible in routine clinical practice due to the high cost and demand for qualified research personnel.

More recently, a mass spectrometry-based technique combined with a single-base extension polymerase chain reaction (PCR) has been used to investigate genotyping across a variety of human cancers [22, 23]. This high-throughput technique, called the MassARRAY platform (Sequenom, Brisbane, Australia), can access up to 40 single-nucleotide polymorphisms in a single reaction with satisfactory sensitivity and specificity. Results from other studies have verified the concordance of genotyping in CRC patient-matched plasma and tumor tissue samples using this mass spectrometry platform [23, 24]. Therefore, in this prospective study, we will use this platform to examine *RAS* mutations in serial blood samples collected from patients with mCRC undergoing cetuximab treatment. To determine a more effective anti-EGFR therapeutic strategy for mCRC, the correlation between the clinical response of tumors to cetuximab and the emergence of resistant mutations will also be analyzed.

## Methods/design

### Study design

This single-arm, non-interventional, uncontrolled, multicenter study will evaluate the emergence of *RAS* mutations in patients with mCRC receiving a cetuximab-based regimen as first-line treatment. In this investigator-initiated study, patients diagnosed with *RAS* wild-type mCRC will be recruited. Patients for whom treatment is planned with a cetuximab-based regimen under the locally approved label will be enrolled. In addition to cetuximab, infusional 5-fluorouracil is required and combination with oxaliplatin or irinotecan is allowed in first-line treatment. On the basis of the best scientific knowledge, clinical practice for each patient is determined entirely by the responsible investigator. This cetuximab-based treatment is expected to continue until disease progression, intolerable toxic effects, or withdrawal of consent. Blood samples from patients enrolled in this study will be collected before the start of cetuximab-based chemotherapy and then every 3 months during first-line treatment. Blood sampling is also required within 3 weeks of disease progression following cetuximab and second-line treatments. The blood samples will be sent to the central laboratory at Taipei Institute of Pathology and evaluated for the *RAS* genotype by using the MassARRAY technique. Pretreatment tissue sections will also be re-evaluated for the *RAS* genotype by using this technique if a discordance of *RAS* genotype occurs between the tissue and blood samples of the same patient. This study is briefly outlined in Fig. 1.

**Fig. 1 Fig1:**
[figure not shown]
Schematic flowchart providing an overview of the study design; wt, wild-type; mCRC, metastatic colorectal cancer; 1 L, first-line treatment; 2 L, second-line treatment; PD, progression of disease

### Study objectives

The primary endpoint is the percentage of *RAS* mutations detected in the cfDNA of patients with mCRC during first-line cetuximab treatment. The secondary objectives are the following endpoints: 1. duration between the start of cetuximab treatment and the new detection of a *RAS* mutation; 2. percentage of mutated alleles detected at disease progression; 3. clinical responses and metastasis resection rates during first-line cetuximab treatment; 4. progression-free and overall survival of patients receiving first-line cetuximab treatment; 5. correlations between *RAS* resistance mutations after cetuximab treatment (occurrence and levels) and clinical survival outcomes; 6. total cetuximab dosage in first-line treatment; and 7. correlations between irinotecan or oxaliplatin dosage and acquired resistance to cetuximab.

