#### Inclusion criteria

Patients with mCRC for whom a cetuximab-based regimen is planned as first-line treatment after considering routine clinical practice, the locally approved label, and the best scientific knowledge. The choice of the chemotherapy regimen for first-line treatment is also at the sole discretion of the investigator, based upon routine clinical practice.Patients aged 20 years and above.Patients pathologically and molecularly diagnosed with wild-type *RAS* CRC.Patients willing to provide blood samples during the study.Patients willing and able to provide signed informed consent.

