#### Exclusion criteria

Patients with a history of any anti-EGFR therapy.Contraindications to cetuximab as per the locally approved label.

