### Sample size calculation

The present study aims to identify the frequency of *RAS* mutations in cfDNA during cetuximab treatment. In earlier studies, 21 and 33% of patients with *RAS* wild-type CRC at baseline displayed *KRAS* mutations at week 24 and 26, respectively [13–15]. Sample size is based on test power considerations by using a confidence limit. When the Wilson score method was used, a sample size of 110 produced two-sided 95% confidence intervals (CIs) of 0.169, 0.176, and 0.180 when the sample proportion was 0.300, 0.350, and 0.400, respectively [25]. Taking a 10% dropout rate into account, 120 patients should be enrolled in this study.

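### The primary RAS percentage has no wild-type baseline cfDNA condition, so as written it mixes pre-existing with newly acquired mutations

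*Protocol article*

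**What the plan says.** All references are to the protocol article.

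- **Aim (Study design).** The study "will evaluate the emergence of *RAS* mutations in patients with mCRC receiving a cetuximab-based regimen as first-line treatment".
- **Primary endpoint (Study objectives; the Abstract agrees in substance).** "The primary endpoint is the percentage of *RAS* mutations detected in the cfDNA of patients with mCRC during first-line cetuximab treatment". It does not require the mutation to be new or the baseline plasma to be wild-type.
- **Entry (Inclusion and Exclusion criteria).** The RAS criterion is "Patients pathologically and molecularly diagnosed with wild-type *RAS* CRC". The exclusions are "Patients with a history of any anti-EGFR therapy" and label contraindications to cetuximab. None of these concerns baseline cfDNA.
- **Sampling (Study design).** Blood is "collected before the start of cetuximab-based chemotherapy and then every 3 months during first-line treatment", and the samples go to the central laboratory for RAS genotyping. Baseline plasma status will therefore be known.
- **Discordance (Study design; RAS mutation analysis of cfDNA and tissue samples).** Pretreatment tissue is re-tested "if a discordance of *RAS* genotype occurs between the tissue and blood samples of the same patient". No consequence for enrolment or analysis is stated.
- **Analysis (Statistical analysis).** The RAS frequency is given with a 95% CI for the efficacy population, defined by at least 8 weeks of treatment and at least one post-baseline RAS mutation in cfDNA. Baseline plasma status plays no part.
- **Contrast.** The first secondary endpoint (time from the start of cetuximab) and the Kaplan–Meier analysis of onset are both confined to mutations that are *new* or *newly detected*.

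**The concern.** A wild-type diagnosis at entry does not guarantee wild-type plasma at baseline. The protocol recognises this: it provides for tissue and blood to disagree, and its Background argues that cfDNA reflects both primary and metastatic sites and avoids limits of tissue testing. Some enrolled patients may therefore carry a detectable plasma RAS mutation before the first cetuximab dose.

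Under the stated definition, such a patient who is positive again at 3 months enters the numerator. The protocol's own onset analysis would not treat that mutation as newly detected. The primary percentage and the onset curve would then describe different events, and the one lacking the restriction is the one meant to answer the emergence question.

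The headline estimate is affected first. The problem also carries over to the Cox and Kaplan–Meier comparisons by mutation status, and to the secondary objectives on resistance mutations and acquired resistance, if they use the same unrestricted status. The Background and Discussion separate primary from acquired resistance; this endpoint does not.

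**Working it through.** **1. The plan's own precision figure.** Sample size calculation gives n = 110 and Wilson 95% interval sizes of 0.169, 0.176 and 0.180 at proportions 0.30, 0.35 and 0.40. Read as full widths:

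width = 2z·√[p(1−p)/n + z²/(4n²)] / (1 + z²/n), with z = 1.96.

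At n = 110 this gives 0.1689, 0.1755 and 0.1801, which reproduces the stated values. The half-width at p = 0.30 is 0.1689/2 ≈ 0.084, or about 8.4 points.

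**2. Inputs for the bias.**
- e = true emergence among patients with wild-type baseline cfDNA. I use 0.30, the first of the plan's sizing proportions.
- b = share of patients with RAS-mutant baseline cfDNA. The documents do not give it; assumed 5%, 10% and 15%.
- r = share of those patients detected again on treatment. Also not given; r = 1 is the upper bound and r = 0.5 a middle case.
- The denominator is taken as all patients with a post-baseline cfDNA result. Read literally, the efficacy population admits only patients with a post-baseline RAS mutation, and the percentage would be 100% whatever b is.

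**3. Formula.** The baseline sample is not itself an on-treatment detection, so baseline positives enter the numerator only if detected again:

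reported = b·r + (1−b)·e; bias = b·(r − e).

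**4. Results at e = 0.30.**

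| b | reported, r = 1 | bias (points) | reported, r = 0.5 | bias (points) |
|---|---|---|---|---|
| 5% | 0.05 + 0.95×0.30 = 33.5% | 3.5 | 0.025 + 0.285 = 31.0% | 1.0 |
| 10% | 0.10 + 0.90×0.30 = 37.0% | 7.0 | 0.05 + 0.27 = 32.0% | 2.0 |
| 15% | 0.15 + 0.85×0.30 = 40.5% | 10.5 | 0.075 + 0.255 = 33.0% | 3.0 |

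The bias is upward whenever r exceeds e. Only b = 15% with full re-detection exceeds the 8.4-point half-width; b = 10% with full re-detection comes close.

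**5. Precision after restriction.** Starting from 110 evaluable patients and removing 5%, 10% or 15% leaves 104, 99 or 94. The Wilson widths at p = 0.30 become 0.174, 0.178 and 0.182, against 0.169 planned.

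**The case against.** The strongest reply is that this is a journal article with a one-line endpoint, and that the handling of baseline-positive patients may sit in the full protocol or SAP. The surrounding text points to the intended meaning: the aim is emergence, the onset endpoint concerns new detection, and a pre-treatment sample is drawn that lets old and new mutations be separated. Nowhere does the article say outright that a pre-existing mutation is to count as emergent.

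That last point stands, and limits the charge to what follows from the definition as written. The rest does not remove it. The article itself states the primary endpoint, the analysis population and the primary analysis, and it uses the restriction for the secondary endpoint but not for the primary one. That is a definition fixed badly, not a detail left out.

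It is also fair to object that the size rests on two unknown quantities and that full re-detection is the worst case. This stands too; at half re-detection the bias is 1 to 3 points, well inside the planned half-width.

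A reader might infer two further faults that the documents do not support:

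- *The result cannot be compared with the rates used for sizing.* Sample size calculation describes those earlier rates as being "of patients with *RAS* wild-type CRC at baseline displayed *KRAS* mutations at week 24 and 26". It does not say that wild-type status was established in plasma. If the earlier studies selected on tissue, the unrestricted percentage could be the closer match. The article does not settle this.
- *The tissue re-test moves patients in or out of the analysis depending on outcome.* The article provides for a repeat genotype and nothing more. No rule reclassifies or removes anyone.

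**Conclusion.** The point holds as a defect of definition. As written, the primary percentage counts any RAS mutation detected in cfDNA on treatment, including one already present in plasma before cetuximab. It therefore does not cleanly measure the emergence the study is meant to evaluate, and it departs from the restriction used for the secondary onset endpoint.

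The size cannot be determined from the documents. For an assumed baseline plasma-positive share of 5% to 15% and true emergence of 30%, the overstatement runs from 1.0 to 3.0 points if half of those patients are detected again, and from 3.5 to 10.5 points if all are. That is from a small fraction of the planned half-width to somewhat above it. If very few patients are plasma-positive at baseline, the effect is negligible.

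The sample size figures themselves reproduce and are not in question. The definition should be corrected because the remedy is cheap and the ambiguity falls on the primary result.

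**What to change.** Reword the primary endpoint and its analysis set in Study objectives, Statistical analysis and the Abstract:

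- **Numerator:** patients with a RAS mutation newly detected in cfDNA during first-line cetuximab, after a RAS wild-type baseline cfDNA sample.
- **Denominator:** patients with an evaluable RAS wild-type baseline cfDNA sample and at least one post-baseline cfDNA *result*. This also replaces the literal requirement of a post-baseline *mutation*, under which the percentage could only be 100%.
- **Baseline-positive patients:** report their number and later course as a separate descriptive group.

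The pre-treatment sample is already drawn and genotyped, so the change is one of wording. The cost is a smaller denominator: at p = 0.30, losing 5% of 110 patients widens the Wilson interval from 0.169 to about 0.174, and losing 15% widens it to about 0.182. Patients without an evaluable baseline sample also leave the primary analysis, so their number should be reported.

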### Eligibility criteria

In this multicenter study, we intend to enroll 120 patients with wild-type *RAS* mCRC from four participating hospitals, namely Kaohsiung Medical University Hospital, Taipei Veterans General Hospital, Cathay General Hospital, and National Cheng Kung University Hospital. The selection of patients is at the discretion of the investigator. Inclusion and exclusion criteria are listed below.

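### Entry among eligible patients is left to investigator discretion, which permits selection error that the confidence interval for the primary single-arm proportion does not cover

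*Protocol article*

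**What the plan says.** All references are to the protocol article.

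- **Eligibility criteria** names the four hospitals and the target of 120 patients, then sets the entry rule: "The selection of patients is at the discretion of the investigator". The next sentence adds: "Inclusion and exclusion criteria are listed below".
- **Inclusion criteria** asks for a planned first-line cetuximab-based regimen, age 20 or over, RAS wild-type disease, willingness to give blood samples, and consent. It separately leaves the choice of chemotherapy regimen to the investigator.
- **Exclusion criteria** has two items: "Patients with a history of any anti-EGFR therapy.Contraindications to cetuximab as per the locally approved label".
- **Study design** describes the study as follows: "This single-arm, non-interventional, uncontrolled, multicenter study will evaluate the emergence of" RAS mutations. It also says: "Patients for whom treatment is planned with a cetuximab-based regimen under the locally approved label will be enrolled".
- **Study objectives** makes the primary endpoint the percentage of RAS mutations "detected in the cfDNA of patients with mCRC during first-line cetuximab treatment". Seven secondary objectives follow.
- **Sample size calculation** restates the aim, "The present study aims to identify the frequency of *RAS* mutations in cfDNA during cetuximab treatment", and sizes the study on interval precision alone: "a sample size of 110 produced two-sided 95% confidence intervals (CIs) of 0.169, 0.176, and 0.180 when the sample proportion was 0.300, 0.350, and 0.400".

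**The concern.** A proportion from a single group with no comparator depends on how patients enter that group. The article states how they enter: the investigator selects, and the listed criteria apply as well. Those criteria set no limit on disease burden, performance status or life expectancy, so discretion has wide room to act.

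Selection could plausibly track the endpoint in two ways. Blood is drawn every 3 months on treatment and again at progression (Study design, Schedule of assessments), so a patient expected to stay on treatment longer has more occasions to test positive. The Background also notes that tumour-derived DNA is often a small part of all circulating DNA, so the amount of disease may affect detection. An investigator can form a view on both at enrolment.

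The primary percentage is at stake. A Wilson interval describes sampling error around whatever group was enrolled, and more patients do not correct a shifted sample. The Discussion faults earlier studies for small size and retrospective design, and the Abstract expects the results to give practical guidance. Both raise the importance of a defensible route of entry.

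**Working it through.** **1. The plan's own precision.** Inputs from Sample size calculation: n = 110, two-sided 95%, p = 0.300, 0.350, 0.400. The full Wilson width without continuity correction, with z = 1.96, is

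width = 2z·√[p(1−p)/n + z²/(4n²)] / (1 + z²/n).

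For p = 0.30: 2 × 1.96 × √(0.001909 + 0.000079) / 1.0349 = 0.1689. For p = 0.35 the width is 0.1755, and for p = 0.40 it is 0.1801. These match the stated 0.169, 0.176 and 0.180, which are therefore full widths. The half-widths are 0.0845, 0.088 and 0.090.

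**2. What selection could do.** Let r be the chance of enrolment for an eligible patient who will become positive, relative to one who will not. The documents give no value for r, so every value below is an assumption. The expected observed proportion is

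p_obs = p·r / (p·r + 1 − p).

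For a true p = 0.30 (half-width 0.0845):

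| r (assumed) | Calculation | p_obs | Shift | Against 0.0845 |
|---|---|---|---|---|
| 0.5 | 0.150/0.850 | 0.176 | −0.124 | outside |
| 0.67 | 0.201/0.901 | 0.223 | −0.077 | just inside |
| 0.8 | 0.240/0.940 | 0.255 | −0.045 | inside |
| 1.25 | 0.375/1.075 | 0.349 | +0.049 | inside |
| 1.5 | 0.450/1.150 | 0.391 | +0.091 | just outside |
| 2.0 | 0.600/1.300 | 0.462 | +0.162 | outside |

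For a true p = 0.35 (half-width 0.088), r = 0.67 gives 0.265 (shift −0.085, just inside) and r = 1.5 gives 0.447 (shift +0.097, outside).

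**3. Effect on the interval.** With n = 110 and a true 0.30, the Wilson interval around the expected value at r = 1.5 runs from 0.305 to 0.485 and misses 0.30. At r = 0.67 it runs from 0.155 to 0.309 and still contains it.

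**4. How large r might be in practice.** An investigator cannot see a future mutation, only a baseline trait related to it. Suppose (assumed) that a trait is present in half of patients, with mutation risk 0.40 in carriers and 0.20 in the others, so 0.30 overall. If carriers are enrolled twice as readily, they make up 2/3 of the sample, and p_obs = (2/3)(0.40) + (1/3)(0.20) = 0.333, a shift of 0.033. That corresponds to r = (0.333/0.667)/(0.30/0.70) = 1.17. To reach r = 1.5 (p_obs = 0.391) through this trait, the carrier share would have to be (0.391 − 0.20)/0.20 ≈ 0.957, a preference of about 22 to 1. A trait more strongly related to the outcome would need less.

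**The case against.** The strongest reply is that the sentence may mean only that the investigator decides who is a candidate for cetuximab. That would be normal in a non-interventional study. Study design says that patients with such a plan will be enrolled, and the inclusion criteria describe regimen choice as also resting with the investigator. This reading is possible but not the natural one. The sentence speaks of selecting patients and stands apart from the criteria, and regimen choice is dealt with separately.

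Second, large ratios act directly on an outcome that does not yet exist, and moderate selection on a baseline trait moves the result by only a few points. This stands, and it limits the likely size. It does not remove the exposure.

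Third, a condensed article commonly leaves screening logs to the full protocol. This also stands: the absence of a log is not the point. The point is the entry rule that the article does state.

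A reader might go further in several ways that the documents do not support:

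- That the sample is hand-picked, or the choice unrecorded. The text allows selection. It does not show that selection occurs or that it goes unlogged.
- That the article itself ties detection in this study to tumour burden. The heavy-burden remark in the Background concerns standard sequencing of the Sanger type. The Discussion calls the sensitivity of the MassARRAY platform comparable to that of digital PCR.
- That the result should represent all first-line RAS wild-type patients. The study's own target is narrower: patients already planned for first-line cetuximab. That entry condition is not a defect.

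**Conclusion.** The point holds as a permitted risk to the primary estimate. The stated rule allows selection among eligible patients, the design has no comparator to offset it, and the planned interval does not include it. The documents fix neither direction nor size.

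It would be tempting to conclude that selection bias matches or exceeds the planned precision. The arithmetic does not bear that out in general. For a true 0.30, ratios of 0.8 to 1.25 stay well inside the half-width, 0.67 stays just inside, and 1.5 falls just outside. Only assumed ratios of about 1.5 or more, or as low as 0.5, carry the true value out of the expected interval. The trait example suggests that such ratios need either strong preference or a strong predictor.

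This is a low-cost improvement worth making. It does not show the study to be invalid, and it changes no sample-size figure. The definition of the efficacy population under Statistical analysis bears on the same percentage, but it is a separate matter.

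**What to change.** Replace the discretion sentence under Eligibility criteria with: *At each hospital, all consecutive patients planned for first-line cetuximab who meet the inclusion and no exclusion criteria are offered participation until 120 are enrolled.* Report the number of eligible patients not enrolled beside the primary percentage.

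If enrolment is already under way, limit the inference to the enrolled sample and say so where the percentage is reported.

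Treatment choice stays with the investigator, and the target of 120 is unchanged. The cost is one amended sentence and a simple count at each of the four hospitals, with slight extra site paperwork.
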